## Abstract

**Background:**

The majority of obese subjects are treated by primary care physicians (PCPs) who often feel uncomfortable with the management of obesity. In a previous study, we successfully developed, implemented and evaluated an obesity management system based on training and coaching of health professionals of family medicine groups (FMGs) by a team of experts in obesity management. Using a pre/post design, this study suggested a positive impact on health professionals’ perceptions and reported obesity care. The current research project is aimed at evaluating the impact on obesity screening and care of this integrated obesity management system. We hypothesize that our program combining preceptorships with a virtual community and on-site coaching will improve: (1) management and weight loss of obese/overweight subjects treated by PCPs for hypertension, type 2 diabetes or impaired glucose tolerance; and (2) screening and initial management of obesity among a regular follow-up group of patients of PCPs who practice in FMGs.

**Methods/Design:**

Ten FMGs will be approached for a practice monitoring project and will be randomised to receive the intervention developed in our previous project or will only be provided clinical practice guidelines. In the participating FMGs, we will enrol 22 patients per FMG with weight related targeted disease and 24 patients with regular follow-up. These patients will be evaluated for the care they received regarding screening and/or management of obesity using medical chart reviews, and will fill out a questionnaire on their lifestyle and satisfaction. They will also be examined for anthropometric measures, vital signs, blood markers for chronic diseases and physical fitness. The same patients will be assessed again after 18 months. The impact of the program on health professionals will be evaluated at baseline, and at 1 year. Qualitative data will also be collected from both professional and patient participants. Direct and indirect costs and QALYs will be evaluated as indicators of cost-effectiveness.

**Discussion:**

In the context of the dramatic increase in obesity prevalence and the low perception of PCPs’ self-efficacy, providing efficient strategies to PCPs and interdisciplinary health care teams for management of obesity is crucial.

**Trial registration:**

Clinicaltrials.gov Identifier: NCT00991640

## Background

### Obesity and management recommendations

Obesity is a major public health problem that was identified as an epidemic by the World Health Organization (WHO) and is associated with multiple co-morbidities, including type 2 diabetes (DM2), hypertension (HTN), cardiovascular disease and cancers [1]. As of 2004, nearly 60% of the Canadian population was reported as being overweight or obese [2]. Over the last 18 years, the proportion of the population considered to be obese has increased by 53% in Canada, but fortunately, the prevalence now seems to have stabilized [2]. Overweight and obesity affect all age groups, including approximately 1 out of 4 children and adolescents [2–4]. The direct cost of obesity in Canada was recently estimated at 4.3 billion dollars, in addition to 5.3 billion dollars related to sedentary lifestyles: these costs represent 4.8% of the global Canadian health care system’s budget [5]. Nonetheless, moderate weight loss in obese subjects has been proven to markedly ameliorate DM2, blood pressure, lipid profile and may decrease mortality [6–10].

In response to the alarming evolution of obesity in Canada, the 2005 federal budget provided $300 million over 5 years for a strategy focusing on healthy living and prevention of chronic disease [11]. Moreover, from 2006 to 2012, the Government of Quebec undertook an important action plan to promote healthy lifestyles and to prevent obesity related health problems. This program, called “Investing in the future”, consists of interventions aiming to: i) promote healthy nutrition, physically active lifestyles and favorable social norms; ii) improve services for overweight and obese individuals and; iii) encourage research and knowledge translation. Their goals for 2012 are to reduce by 2% the prevalence of obesity and that of overweight by 5%, among children and adults in Quebec [12]*.* Our research proposal is thus completely in line with these objectives and is developed in partnership with our local health agency (ASSSE) and the Quebec Ministry of Health (MSSS).

The “2006 Canadian Clinical Practice Guidelines on the Management and Prevention of Obesity in Adults and Children” (CCPGO) emphasize the importance of a multidisciplinary health care team for weight management and include evidence-based key recommendations for the clinical management of obesity [4]. They suggest a stepwise obesity and overweight management algorithm which can be applied in primary care. Furthermore, CCPGO put a special emphasis on the need for research to develop and evaluate the organization of care for overweight and obese individuals and also on the need for continuing education to focus on activities that provide physicians and health professionals with the skills to counsel people confidently. Our project is in line with these guidelines and will also help in appropriate knowledge transfer of the CCPGO that is needed in order to implement them in clinical practice.

### Inter-professional collaboration and organization of primary health care services

The implementation of family medicine groups (FMG) in 2001 resulted in major organizational changes in primary health care services in Quebec [13]. A FMG is a group of family physicians who practice together in collaboration with nurses and other health care professionals and are responsible for ensuring primary care services 24/7 in a given territory. Improved accessibility and continuity, interdisciplinarity and patient registration are central principles of that reorganization. FMGs provide further opportunities to improve care for specific conditions that warrant lifestyle modifications and call for interventions that are based on inter-professional collaboration. This construct refers to individuals from distinct disciplinary backgrounds, who work together to achieve a common goal. In today’s delivery of health care services where different professionals, especially physicians and nurses, are bound to work together, a collaborative approach may enhance quality of care and quality of life for patients [14–16]. A collaborative approach also involves patients and is reputed to promote their empowerment giving them the support to i) mobilize their resources; and ii) focus on their strengths allowing them to take charge of their situation [16]. Thus, obesity represents a special challenge that is increasingly addressed in some FMGs and benefits from a collaborative approach as outlined in the CCPGO [4,17].

### Models of care for chronic disease

The chronic care model (CCM) was developed and validated by the MacColl Institute for Healthcare Innovation and constitutes an organizational approach to caring for people with chronic disease [18,19]. It describes practical, supportive, evidence-based interactions between an informed, activated patient and a prepared, proactive practice team. The CCM identifies essential elements of a health care system that encourage high-quality chronic disease care including: the community; the health system; self-management support; delivery system design; decision support, and clinical information systems [18,20,21]. A meta-analysis of 112 studies has shown that interventions that contained one or more CCM elements improved clinical outcomes and processes of care [22]. This framework was used to develop our intervention.

It was complemented by a theoretical model for changing lifestyle behaviour developed by Maryon-Davis: the Three ‘*Es*’ Model which includes *Encouragement*, *Empowerment* and *Environment* [23]. Encouragement refers to support patient efforts to change their lifestyle mainly in regard to diet and physical activity. This support can be provided by allied health professionals, primary care physicians (PCPs) or even through media and social programs. Encouragement needs to be supported by empowerment, which is based on patient education and the acquisition of effective skills to concretely modify behaviour. The third E, which may be the most important, refers to the alliance of the cultural, social, physical and economic environments required to assist in lifestyle factor improvements such as nutrition and exercise. Interestingly, this model can also be applied to PCPs: increasing their knowledge, giving them accurate ways to manage obesity and offering them the support of an expert team as ways of increasing their self-confidence and self-efficacy which should ultimately have positive effects on their clinical practice and patients.

Thanks to inter-professional collaboration, expert-supported FMGs are an ideal setting for obesity management according to CCM and the Three “Es” Models as they can provide education, support and regular follow-up to patients within the health care system.

### Obesity management in primary care

Considering the growing prevalence of obesity, the majority of patients should be managed by primary care givers. Unfortunately, PCPs and health professionals often feel that they are unable to help their patients lose weight and their self-efficacy in obesity treatment is poor [24,25]. As a result, obesity tends to be neglected when compared to other chronic conditions like hypertension and diabetes. When auditing medical records from PCPs, obesity is definitely underreported and recommendations for weight control interventions are reported even less [26,27]. It stands to reason that if obesity is not mentioned in a patient’s record, it is unlikely that any intervention is ongoing. This only highlights the need for major changes with respect to medical practice regarding this important health problem.

Since 2004, a United Kingdom team set up a programme for weight management in primary care: the “Counterweight Programme” [26]. They recruited a total of 80 practices from seven different regions of the United Kingdom, of which 18 were randomly assigned to act as controls. In each practice of the intervention group, 50 obese and 50 age- and sex-matched normal weight patients were selected for a total of 1906 patients. At baseline, less than 58-71% of patients had a BMI measurement and only 13-16% of obesity diagnoses were recorded, supporting suboptimal screening and under-reporting of this condition in primary care. Primary care nurses (PCNs) were identified as the most suitable individuals to deliver the weight management intervention and received 12 h of training followed by 6 months of mentoring. The PCNs were encouraged to see patients previously referred by PCPs for six individual appointments or for six group sessions during a period of three months followed by quarterly meetings. Evaluation of the impact of the interventions on patients was then made at 12 and 24 months. Forty-nine percent of patients were considered as completers of the programme (based on follow-up compliance). At 12 months, 40% of completers and 33% of all patients followed-up (including non-completers) achieved a ≥5% weight loss that was mostly maintained at two years. This suggests that empowerment and education of patients in a primary care setting can have a successful impact on modification of their health behaviour and weight.

### Electronic tools in obesity management

Coupling a preceptorship with a virtual learning community (as further described below) and specific tools for the practice setting can be key ingredients to effect change in practice. Internet based communication, accessed at one’s own time in the clinic or at home, or used for same-time meetings, is transforming the continuing information environment. *e*Learning is becoming increasingly popular and has been proven to be at least as effective as classical continuing medical education (CME) to improve knowledge, and may initiate changes in medical practice [28].

This learning web-based architecture supports different dimensions and different theoretical considerations, including cognitive, educational, organizational, sociological, technical and other disciplines, all of which underlie the creation of this architecture. The various actors, specialists and community care givers, physicians, nurses, nutritionists and other team members, patients and their families make up a learning community. The term “virtual learning community” has recently gained common use where supported by web based communications [29–31]. It defines the cooperative process and is not restricted to structured courses. They follow integrative global objectives and require facilitation and technical expertise if they are to be sustained. Potential advantages of an *e*Learning community include a more fluid communication across the different actors enabling consensus or resolving of complex situations as well as flexibility with respect to different working environments and ethos [29–31].

### Contributions from our group and preliminary data

Our group has implemented an interdisciplinary approach to obesity care management since 2001. Our interdisciplinary team includes nurse-clinicians, dietitians, a psychologist, kinesiologists and several endocrinologists. It offers, under the coordination of the nurse-clinician, a variety of behavioural and motivational approaches to lifestyle modification through a series of group seminars in addition to individual consultations with health professionals every 6 weeks, or as needed. To our knowledge, such a system without out of pocket costs to the patient is almost unique in Canada. Prospective studies of obese patients with metabolic co-morbidities managed by our multidisciplinary team reveal that 45-55% lose 5% or more of their initial body weight after 12 months in our program [32,33]. This is accompanied by important metabolic benefits [33,34]. The effectiveness of our intervention is thus comparable to other effective but more intensive and costly interventions [8,9,35], making it more feasible in the context of the Canadian health care system.

We have developed a model, based on the chronic care model, emphasizing the importance of primary care supported by regional experts, to improve obesity management throughout the continuum of care (Figure 1). In 2005, we obtained a first CIHR-PHSI grant to develop, implement and evaluate an obesity management system based on preceptorships in combination with a virtual community favouring continuous support of FMGs by our expert team [36]. This program aimed to enhance primary care teams’ expertise and attitudes with respect to obesity management, foster the implementation of nurse-coordinated team management for obesity in primary care settings, and improve access to quality support resources for PCPs and their teams, as well as their patients. Thirty-eight participants (13 nurses, 25 MDs) from 8 FMGs were enrolled in the project [37] and evaluated at baseline and 1 year later.

**Figure 1 Fig1:**
[figure not shown]
**Model of integrated obesity management.**

After an extensive needs assessment, a 2-day preceptorship was developed combining interactive sessions with experts, case discussions and observation of real patient encounters [38]. The preceptorship was validated and remodeled with the participation of one of the FMGs before being offered to all participants. A web-based portal with professional and patient tools in association with monthly interactive on-line educational activities for health professionals was implemented in tandem with preceptorships as the key ingredients used to effect change in practice [39].

Health professionals’ confidence level, attitude toward obese individuals and perception of self-efficacy to advise on exercise and diet improved after the preceptorships and these improvements were maintained 1 month and 1 year after as compared to baseline [25]. Clinical practice also seemed to improve with an increase in self-eported waist circumference measurement, evaluation of patient readiness to change and suggested use of a pedometer and food diary [25].

Our next step is now to evaluate the impact on health professionals’ clinical practice and patient-related outcomes of such an integrated model of obesity management and to move from a pre-post design to the stronger design of a randomized-controlled trial (Phase-2).

### Hypothesis

We hypothesize that our program combining preceptorships with a virtual community (intervention) will improve: (1) screening and initial management of obesity among unselected patients of PCPs who practice in FMGs; and (2) management and weight loss of obese and overweight subjects who are treated by PCPs for HTN, DM2 or impaired glucose tolerance (IGT). We further hypothesize that: (3) these benefits will be achieved through improvement of primary care providers’ confidence and competence in managing obese patients, as well as changes in their clinical practice of obesity care; (4) patients will express better satisfaction regarding their management; and (5) our research program will result in generalizable and transferable new knowledge useful for decision-makers of the healthcare system.

### Aims of the study

#### Primary aims

Among patients who are regularly followed by a PCP for weight-related diseases targeted for lifestyle management (HTN, DM2 or IGT) and with a BMI ≥ 25 (*targeted diseases group*), we aim at improving, after 18 months of participation in our program (vs. control):the proportion of subjects who have an initial weight management intervention planned;the proportion of subjects who lose at least 5% of their initial weight;weight, waist circumference, lean body mass, blood pressure, physical fitness level, physical activity level and healthy eating habits;biochemical markers of metabolic control and cardiac risk (HbA1c, ApoA and ApoB).
Among patients who are regularly followed-up by a PCP for other health conditions (*regular follow-up group*), we aim at improving after 18 months of participation in our program (vs. control):the proportion of patients who have measured weight, BMI and waist circumference;the proportion of overweight or obese subjects who have an initial intervention planned;weight, waist circumference, lean body mass, blood pressure, physical fitness level, physical activity level, healthy eating habits and markers of metabolic control in overweight or obese subjects.

#### Secondary aims

3.Among health professionals who receive the intervention (vs. those who did not), we aim at:ameliorating their attitudes and perceptions towards patients and treatment effectiveness;improving their perception of self-efficacy in managing obesity;increasing their knowledge and expertise on obesity management; andchanging their practice.
4.Among patients who are followed by PCPs (both targeted disease and regular follow-up groups) who receive the intervention (vs. control), we aim at:evaluating their attitudes and perceptions regarding obesity/overweight and lifestyle; andimproving their satisfaction regarding their management.
5.Evaluate costs and indicators of cost-effectiveness of the intervention.6.Transfer knowledge to intervening parties and decision-makers of the health system using embedded knowledge transfer to patients, health professionals and decision-makers in addition to traditional end-of-grant strategies.

## Methods/Design

### Research design

A schematic representation of research design is presented in Figure 2.

**Figure 2 Fig2:**
[figure not shown]
**Summary of design of the proposed research project.**

#### Study participants

The Integrated University Health Network, known as the RUIS (*Réseaux universitaires intégrés de santé*), of *Université de Sherbrooke* caters to a population of over 1 million people, encompassing a vast territory including Sherbrooke and Montérégie areas. A pool of at least 35 FMGs in this coverage area did not participate in our Phase-1 project. We will enroll a total of 10 of these FMGs in Phase-2, from which 4-10 members (including at least 2 PCPs and 1 nurse) will participate in our study. When we will initially contact FMGs, we will propose to them a study assessing lifestyle management in primary care and its evolution over time. When we will be in contact with 2 interested FMGs, we will randomize them to the intervention or control groups. The first FMG will then be offered to participate in our obesity management system with preceptorships and virtual learning community. The control FMG will be offered practice monitoring without being aware of the intervention. Participants of each group will sign different consent forms.

As much as possible, we plan to evaluate participants from FMGs pairs of intervention and control groups concomitantly in order to avoid bias related to time of evaluation (due to seasonal effects on weight, campaigns of health promotion, high-impact scientific publications, etc.). Within each FMG, adult patients who present for follow-up will be offered by FMG clerical personnel to have their chart accessed by our team and to be contacted if eligible for the project. If they consent, their chart will be screened to verify if they had, during the past 2 years, at least 4 documented visits for the targeted disease group and at least 2 visits for the regular follow-up group, and if continued follow-up is planned or highly probable in the next 18 months. We aim to include in our study 22 patients per FMG in the targeted disease group, and 24 patients per FMG in the regular follow-up group (total of 460 patients). Patient numbers will be prospectively accrued within each patient category during the recruitment period and before preceptorship delivery for the intervention group, until targeted numbers are achieved. In order to minimize important potential biases, patients will be kept blinded regarding their FMG group and the study objectives related to the evaluation of this intervention.

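### FMGs are randomised before professionals consent and, by clear implication, before patients are enrolled, so professionals volunteer for different offers and those who recruit patients are not stated to be masked

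*Protocol article*

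**What the plan says.** The order of events is in the protocol article, Research design, Study participants.

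- **First contact.** FMGs hear only of a monitoring study: "we will propose to them a study assessing lifestyle management in primary care and its evolution over time".
- **Randomisation.** It follows as soon as a pair is available: "When we will be in contact with 2 interested FMGs, we will randomize them to the intervention or control groups".
- **Offers.** They are made after allocation and differ by arm. For the intervention side: "The first FMG will then be offered to participate in our obesity management system with preceptorships and virtual learning community". For the other side: "The control FMG will be offered practice monitoring without being aware of the intervention".
- **Consent.** "Participants of each group will sign different consent forms".
- **Professionals.** Only some members of each FMG take part: "from which 4-10 members (including at least 2 PCPs and 1 nurse) will participate in our study".
- **Patient approach.** "Within each FMG, adult patients who present for follow-up will be offered by FMG clerical personnel to have their chart accessed by our team". The research team then screens the charts on visit counts and on how likely follow-up is to continue for 18 months.
- **Patient accrual.** "Patient numbers will be prospectively accrued within each patient category during the recruitment period and before preceptorship delivery for the intervention group".

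The same section says that patients are kept blind to their FMG's group. The Intervention section says that members of the research team give the training sessions. Under Sample size, data analysis and interpretation, patients are compared by the allocation of their FMG, PCPs are compared by whether they received the intervention, and multivariate adjustment for baseline differences and FMG clustering is planned.

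**The concern.** Randomising FMGs makes the arms comparable only if the people measured within them are identified independently of the allocation. Here allocation comes first.

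For professionals the effect is direct. In one arm the volunteers accept a two-day obesity course with a virtual community and coaching. In the other they accept monitoring of their practice. Aim 3 compares attitudes, self-efficacy, knowledge and practice in obesity care, and willingness to take an obesity course is plausibly related to all four.

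For patients the route is narrower. It runs through the people who decide whom to approach and whose chart passes screening. If they know the arm, the patients enrolled could differ between arms, and with them the two primary patient variables: loss of at least 5% of weight (Aim 1) and a reported BMI (Aim 2).

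**Working it through.** **1. Is the order really allocation first?**

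- *Professionals:* yes, explicitly. The offer comes after randomisation and the consent forms are arm-specific, so consent cannot precede allocation.
- *Patients:* by clear implication. Accrual is timed against training in an intervention group that is already designated, and patients are blinded to the group of their FMG, so the group exists when they are enrolled.

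**2. Who can know the arm when patients are recruited?**

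| Party | What the article supports |
|---|---|
| Patients | Blinded; told only of a lifestyle-management study |
| Control FMG staff | Know their own offer; unaware of the intervention |
| Intervention FMG professionals | Know, because they have been offered the programme |
| FMG clerks who make the approach | Not stated; no masking described |
| Research team that screens charts | Runs the pairwise allocation and gives the sessions; no masking described |

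Most screening criteria are counts of documented visits (at least 4 or at least 2 in two years). One is a judgement, the likelihood of continued follow-up, and that is where knowledge of the arm can act.

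**3. Do the stated safeguards close the gap?**

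- Blinding patients stops patients choosing on arm. It does not mask those who approach or screen them.
- Accruing before the preceptorship stops the training itself from changing who is enrolled. It does not stop knowledge of the allocation from doing so.
- Adjustment for baseline differences covers measured factors only.

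**4. The plan's own figure, then an illustration.** The point does not depend on the sample size, but the sample size sets the scale.

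Inputs (Sample size section): 21% v 42%, 80% power, chi-square, 30% loss, α 5%. Two-sided testing is my assumption.

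- n per arm = [1.96·√(2·0.315·0.685) + 0.842·√(0.21·0.79 + 0.42·0.58)]² / 0.21² = 76 after rounding up.
- Total 2 × 76 = 152; 152/0.70 = 218 after rounding up, against 220 stated. The figure reproduces.
- Evaluable per arm: 220 × 0.70 / 2 = 77; power at 77 per arm is 80.7%.

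Now suppose no true effect, and that selection alone raises the rate in one arm by d above 21%. With SE = √{[0.21·0.79 + (0.21+d)(0.79−d)]/77}, the chance that a two-sided 5% test rejects is 1 − Φ(1.96 − d/SE) + Φ(−1.96 − d/SE):

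| d (assumed) | Chance of a false positive |
|---|---|
| 0 | 5% |
| 3 points | 7% |
| 5 points | 11% |
| 10 points | 30% |

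These values ignore clustering. The shifts are assumptions; nothing in the article says which, if any, applies. For a sense of scale, if one arm had 10 percentage points more motivated patients, and the assumed 5% weight-loss rates were 45% in motivated and 20% in other patients, the shift would be 0.10 × (45 − 20) = 2.5 points, or 2.5/21 = 12% of the target difference.

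**The case against.** The strongest reply is that the patient side is already well protected. Clerks hand out a pamphlet to people who present for follow-up, and the trainees do not pick the patients. Eligibility rests mainly on visit counts. Patients are blinded, accrual ends before training, and control FMGs do not know of the intervention. Baseline measures include a readiness-for-change score that could enter the adjusted analysis. The differing consent forms are deliberate, because they keep controls unaware. All of this stands, and it makes the patient part a residual risk. It does not answer the part about professionals, nor the missing masking of recruiters and screeners.

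Three stronger readings are tempting and are not supported:

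- *A refusal of training would remove FMGs from the intervention arm only.* The article does not say that a declining FMG is dropped, and a control FMG can also decline monitoring.
- *Ten FMGs are too few to balance the bias out.* Selection of this kind is systematic, so more FMGs would not balance it either.
- *Patients of untrained colleagues will dilute the effect.* The screening text does not repeat the link to participating professionals, but Aim 4 and the planned correlations with patients' own providers presuppose it. No dilution can be calculated from the article.

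It is also fair that reordering may come too late for some FMGs, since Ethical considerations reports consent and first patient contact in the past tense.

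**Conclusion.** The point holds in a limited form. For professionals the risk is built into the stated sequence: after allocation, each arm volunteers for a different offer, and the Aim 3 comparisons are exposed to that self-selection. The plan to compare PCPs by receipt of the intervention adds to it, because receipt is decided after randomisation.

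For patients, differential recruitment is possible but not shown. A reader might infer that both samples are chosen by people who all know the arm. The article does not support that: patients and control FMGs are unaware, and whether the clerks know is not stated. What can be said is that masking of recruiters and chart screeners is not described, and that the screening team is also the team that delivers the intervention.

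The size of any bias cannot be estimated from the document, and the false-positive rates above only show what assumed shifts would do. The conclusion concerns a sequence that the article states. Masking of recruiters and screeners may be set out in a fuller protocol, so the patient part is held with less confidence than the professional part. This is an avoidable weakness that should be corrected; it does not invalidate the trial.

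**What to change.** For each pair, change the order:

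1. Both FMGs agree to the monitoring study. All participating professionals sign the same initial consent and are listed.
2. Patients are enrolled and baseline-assessed in both FMGs.
3. Only then is the pair randomised, and the programme is offered to the intervention FMG with an additional consent.

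Control FMGs stay unaware and patients stay blinded, as now intended. Analyse FMGs and listed professionals by allocation, including any who decline the training, in place of the comparison by receipt.

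For pairs where reordering is no longer possible, mask to allocation those who approach patients and those who screen charts.

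**Cost.** A procedural and consent-form amendment needing ethics approval. The preceptorship already waits for its own FMG's accrual, so the added delay is the time the faster FMG waits for the slower one to reach 22 + 24 = 46 patients, and preceptorship dates are booked later. That wait falls between baseline and training for patients already assessed, so recruitment within a pair should run as closely in parallel as possible, which the article already intends.
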